### Statistical analysis

Descriptive statistics will be used to present the outcomes of the study parameters and the socio-demographic data. Means and standard deviations will be calculated for variables on an interval scale and medians and interquartile ranges for ordinal variables. Proportions will be calculated for nominal variables.

Subgroup analyses will be performed for patients presenting in UWS versus MCS at baseline and for traumatic versus non-traumatic disorders of consciousness.

The proportions of patients transitioning from UWS to MCS and emergence from MCS to the conscious state will be calculated during and after EIN.

The course of recovery of consciousness (yes/no) over time will be analysed using Generalized Estimating Equations (GEE) analysis for logistic outcomes on an intention-to-treat basis. Assuming that data are missing at random, data imputation is unnecessary in GEE analysis; all observations are taken into account in contrast to complete case analyses. Recovery (yes/no) at each time point will be included as the dependent variable in the GEE model. Separate models will be generated for transitions from UWS to MCS and from MCS to the fully conscious state based on the CRS-R. Independent variables that will be added one by one to the models, include- measurement time (weeks), traumatic vs. non-traumatic aetiology, age at injury, and complications (yes/no or number). Significant predictors (*p* < 0.05) will be included in a multivariable model using a Bonferonni correction, dividing the significance level (alpha< 0.05) by the number of predictors included in the model.

Also using GEE analysis, the course of quality of life (EQ-5D-5L and Qolibri) and participation (CIQ) over time will be analysed using separate linear outcome models. The effects of time, cognitive (MoCa), behavioural (NPI), emotional (HADS), and motor status (FIM), and level of disability (DRS) and discomfort (NCS) on quality of life or participation during follow-up will be studied by adding these time-dependent variables (one by one) as independent variables to the models. Significant predictors (*p* < 0.05) will be added into a multivariable GEE-model to study the independence of these potential predictors on the outcomes using the Bonferroni correction.

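### The Bonferroni divisor counts only the predictors that pass a p<0.05 screen on the same data, so the correction does not guarantee the 5% level it is applied to

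*Protocol article*

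**What the plan says.** All of this is in the protocol article, Methods, Statistical analysis.

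- **Recovery of consciousness.** There are two logistic GEE models: "Separate models will be generated for transitions from UWS to MCS and from MCS to the fully conscious state based on the CRS-R". The listed candidates are "measurement time (weeks), traumatic vs. non-traumatic aetiology, age at injury, and complications (yes/no or number"), each entered singly. Those with p<0.05 "will be included in a multivariable model using a Bonferonni correction", and the correction is defined as "dividing the significance level (alpha< 0.05) by the number of predictors included in the model".
- **Quality of life and participation.** There are separate linear GEE models for EQ-5D-5L, QOLIBRI and CIQ. Seven candidates are screened singly: "The effects of time, cognitive (MoCa), behavioural (NPI), emotional (HADS), and motor status (FIM), and level of disability (DRS) and discomfort (NCS"). Those with p<0.05 go into a multivariable model "to study the independence of these potential predictors on the outcomes using the Bonferroni correction". The divisor is not restated here.

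The section gives no familywise error target in words. It applies a Bonferroni correction to 0.05.

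**The concern.** Bonferroni holds the error rate at 0.05 only if the divisor covers all the tests from which a positive finding could have emerged. Here the one-by-one screen is where most of the testing takes place, and the divisor ignores every candidate that failed it. Two consequences follow from the wording alone:

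1. If exactly one candidate survives, the multivariable model is the single-predictor model already fitted. Its p-value is below 0.05 by selection and the threshold is 0.05/1, so the second step cannot reject it.
2. The threshold is set by the data. A multivariable p of 0.02 counts as significant when two predictors survived (0.05/2 = 0.025) and not when three did (0.05/3 = 0.0167).

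Measurement time is listed among the candidates, so it adds to the divisor when it survives, although it is part of the design of a longitudinal model.

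Predictors of recovery are a declared output of the study (Abstract, Background and Discussion) and are meant to support benchmarking and better prediction of outcome. Readers would take predictors reported under this rule as corrected for multiplicity.

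**Working it through.** **Inputs from the protocol article.** Screen at p<0.05; final threshold 0.05 divided by the number of predictors in the model; m = 4 listed candidates per recovery model; m = 7 per quality-of-life or participation model; planned inclusion of 72 patients (Data collection; used only in the simulation below).

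**Assumptions.** The quality-of-life and participation models use the divisor defined for the recovery models. The number of truly predictive candidates (t) and the correlation among candidates are not given, so both are varied.

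**The nominal level.** With a divisor k fixed in advance, k × 0.05/k = 0.05, so the intended level is reproduced. The question is what happens when the screen chooses k.

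**Formula.** Suppose t true predictors are always retained, the m − t null candidates are independent, and a null candidate's p-value is the same in both steps. Given survival, a null p-value is uniform below 0.05, so with j null survivors it falls below 0.05/(t+j) with probability 1/(t+j). Then

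P(at least one false predictor) = Σ over j = 1 to m−t of C(m−t, j) × 0.05^j × 0.95^(m−t−j) × [1 − (1 − 1/(t+j))^j].

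**Four candidates, none predictive**
- j=1: 4 × 0.05 × 0.95³ = 0.1715, times 1 = 0.1715
- j=2: 6 × 0.05² × 0.95² = 0.01354, times 0.75 = 0.0102
- j=3 and j=4 together: 0.0003
- Sum: 0.182

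**Seven candidates, none predictive**
- j=1: 7 × 0.05 × 0.95⁶ = 0.2573, times 1 = 0.2573
- j=2: 21 × 0.05² × 0.95⁵ = 0.0406, times 0.75 = 0.0305
- j=3 and above: 0.0026
- Sum: 0.290

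Most of each total is the sole-survivor term (17.1% and 25.7%), which does not depend on the same-p-value assumption. With no correction after the screen, the figures would be 1 − 0.95⁴ = 18.5% and 1 − 0.95⁷ = 30.2%. When nothing is predictive, the correction therefore removes almost nothing.

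**With true predictors present (same formula)**

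| True predictors | 4 candidates | 7 candidates |
|---|---|---|
| 0 | 18.2% | 29.0% |
| 1 | 7.2% | 13.4% |
| 2 | 3.3% | 7.8% |
| 3 | 1.3% | 4.8% |
| 4 | – | 2.9% |
| 5 | – | 1.7% |
| 6 | – | 0.7% |

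**Simulation check.** Two-step linear regression, 72 patients, 8,000 runs per setting, equal correlation among candidates. The true predictor has coefficient 0.6 with residual SD 1.

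| Setting | Correlation 0 | 0.3 | 0.6 |
|---|---|---|---|
| 4 candidates, none true | 17.6% | 16.0% | 10.8% |
| 7 candidates, none true | 29.3% | 22.6% | 13.7% |
| 4 candidates, one strong true | 4.8% | 2.3% | 1.9% |
| 7 candidates, one strong true | 8.9% | 2.6% | 1.8% |

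This has one outcome per patient and is not a repeated-measures GEE, so it shows direction and rough size only.

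**Dividing by the number screened.** With no true predictor and independent candidates: 1 − (1 − 0.05/4)⁴ = 4.9% and 1 − (1 − 0.05/7)⁷ = 4.9%. The simulated rate with this divisor was below 5% in every setting tried.

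**The case against.** The strongest reply is that the worst case is unlikely here. The Background names younger age and traumatic aetiology as prognostic factors and cites recovery in traumatic injury rising from 38% at 3 months to 78% at 12 months. Age, aetiology and time are three of the four recovery candidates. One cited study found similar outcomes for traumatic and non-traumatic UWS; if aetiology is set aside, two true predictors remain and the formula gives 3.3%. The EQ-5D-5L items on mobility, self-care, pain and mood overlap with FIM, DRS, NCS and HADS, so three or more true associations with that outcome are plausible. If time is truly related to the outcome and survives, a single noise variable faces 0.025 rather than 0.05. All of this stands, and it limits the size of the problem. It does not repair the rule, because a level that holds only when enough candidates happen to be real is not guaranteed by the correction.

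A reader might go further and infer three things that the document does not support:

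- **Fixed error rates of 7–18% and 13–29% per model.** These are only the cases of one and zero true predictors under independence. The one-predictor values also rest on the same-p-value assumption, and the simulation gave 4.8% and 8.9% in their place.
- **Failure to meet a stated familywise target.** The protocol states none. A 5% level is implied by applying Bonferroni to 0.05.
- **True predictors lost because the rule is too strict.** For the same candidate list, 0.05 divided by the survivors is never stricter than 0.05 divided by the number screened. The valid complaint is that the threshold is arbitrary, not that it is severe.

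The divisor for the quality-of-life and participation models is also an inference, and a fuller plan may define it.

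**Conclusion.** The point holds as a defect in the stated rule for the recovery models, and for the quality-of-life and participation models if the same divisor applies. The correction does not guarantee 5%, and its threshold depends on how many other variables pass the screen. The figures of about 18% and 29% are upper values under independent candidates with no true predictor. Correlation lowers them, and by the formula the rate is below 5% with two or more true predictors of 4, or three or more of 7. Severity is moderate: this is a single-arm observational cohort with descriptive and prognostic aims and no treatment comparison, so the consequence is over-confident naming of predictors.

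**What to change.** Replace the divisor sentence with one that fixes the count in advance: for each outcome, divide 0.05 by the number of candidates screened. Keep measurement time in every model as a design term outside that count. This leaves 3 candidates per recovery model (0.05/3 = 0.0167) and 6 per quality-of-life or participation model (0.05/6 = 0.0083). State that the same rule applies to both groups of models. The count also requires a single coding of "complications (yes/no or number") to be chosen beforehand, so that it is one test.

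An alternative is to fit all pre-specified candidates in one multivariable model per outcome and apply Holm to their p-values, which removes the screen altogether. If neither is wanted, present the predictor analyses as exploratory, with estimates and confidence intervals and no claim of multiplicity correction.

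The cost is one or two sentences and some loss of power when few predictors survive: for a recovery model, 0.0167 in place of 0.05 (one survivor) or 0.025 (two). If all four survived, the present rule would give 0.0125, so in that case the new threshold is slightly less strict.

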## Background

Prolonged disorders of consciousness (PDOC) (> 4 weeks) due to acquired brain injury (ABI) although uncommon [1, 2] have a major impact on patients and their families [3]. Two diagnostic entities are distinguished within PDOC: the unresponsive wakefulness syndrome (UWS, previously known as vegetative state) and the minimally conscious state (MCS) [4, 5]. In UWS, persons display spontaneous eye opening and sleep/wake cycles, but observable signs of purposeful behaviour (e.g. language comprehension, behavioural response to stimuli) are absent [6]. Patients in MCS demonstrate minimal but definitive behavioural evidence of awareness. Conscious behaviour in MCS is often subtle and inconsistent, and must be systematically differentiated from reflexive or random behaviour [6]. Based on the complexity of behaviour, a differentiation is made between MCS-minus (MCS-) and MCS-plus (MCS+) [7, 8]. MCS+ is distinguished from MCS- by the evidence of language processing [7]. PDOC can arise from various aetiologies, but the most common causes in adults are traumatic brain injury, intracerebral and subarachnoid haemorrhage and hypoxic-ischemic encephalopathy [4, 9, 10]. Hypoxic-ischemic encephalopathy is the most common cause in UWS patients (38–50%) [9, 11], while cerebral haemorrhage is most common in MCS [9]. Van Erp et al. reported a prevalence of 0.1 to 0.2 hospitalised and institutionalised UWS patients per 100,000 members of the general Dutch population [11] while worldwide prevalence varies from 0.2 up to 6.1 per 100,000 [1]. PDOC patients may benefit from subacute neurorehabilitation, such as early intensive neurorehabilitation (EIN). EIN focuses on (1) basic care and prevention of complications [12] (e.g. thrombo-embolic disease, contractures, skin breakdown, paroxysmal sympathetic hyperactivity), which cause a substantial raise in morbidity, discomfort and pain, and in healthcare costs [13]; (2) accurate assessment and treatment aimed to facilitate recovery of level of consciousness (LOC); (3) finally, providing comprehensive education and empowerment of families to foster families’ coping.

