### Measurement instruments

#### Coma recovery scale revised (CRS-R)

The CRS-R [29] is a bedside assessment tool for differentiating levels of consciousness by observation of responses to various stimuli. It is composed of 6 hierarchical subscales: auditory, visual, motor, oromotor/verbal, communication and arousal with 23 dichotomously scored items [30]. The item content of the CRS-R identifies ascending levels of conscious behaviour/ability and using a combination of items to differentiate UWS from MCS from emerged from an MCS based on The Multi-Society Task Force on Persistent Vegetative State and Aspen Workgroup criteria [29]. An American Congress of Rehabilitation Medicine practice parameter recommends the use of the CRS-R based on its standardised administration and scoring procedures, item content, and inter-rater and test-retest reliability [26, 29].

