#### Functional Independence measure (FIM)

The FIM measures the level of a patient’s disability and indicates how much assistance is required for conducting activities of daily living [33]. The FIM contains 18 items composed of 13 motor tasks and 5 cognitive tasks. Tasks are rated on a 7-point scale, ranging from 1 = total assistance to 7 = complete independence. FIM total scores range from 18 to 126, with higher scores reflecting a higher level of functioning [34].

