In caregivers, self-efficacy (GSES) and caregiver strain (CSI) are measured, which will also be modelled using GEE analyses. Independent variables added to these models include age and gender of the caregiver and the level of consciousness (UWS, MCS, or conscious), and the cognitive (MoCA) and motor (FIM) status of the patients.

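### FIM enters the quality-of-life and participation models as motor status without level of consciousness, so its one-by-one coefficient mixes the two

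*Protocol article*

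**What the plan says.** All places are in the protocol article.

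- **Quality-of-life and participation models (Statistical analysis).** The outcomes are EQ-5D-5L, QOLIBRI and CIQ, analysed with linear GEE. The covariates are time, MoCA, NPI, HADS and "motor status (FIM), and level of disability (DRS) and discomfort (NCS) on quality of life or participation during follow-up". They are added singly. Those with p < 0.05 go into a multivariable model with a Bonferroni correction.
- **Caregiver models (Statistical analysis).** Besides the caregiver's age and gender, the covariates include "the level of consciousness (UWS, MCS, or conscious), and the cognitive (MoCA) and motor (FIM) status of the patients".
- **FIM section.** The scale "indicates how much assistance is required for conducting activities of daily living". Of its 18 items, 13 are motor and 5 cognitive. On how each item is scored, the section states: "Tasks are rated on a 7-point scale, ranging from 1 = total assistance to 7 = complete independence". It gives 18 as the lowest and 126 as the highest possible total, a high total being the better result.
- **Background.** In UWS, "observable signs of purposeful behaviour (e.g. language comprehension, behavioural response to stimuli) are absent". MCS behaviour is described as definite but often subtle and inconsistent.
- **EQ-5D-5L section.** A proxy completes the questionnaire until the patient regains consciousness, so unconscious patients do contribute outcome data.

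**The concern.** Every patient enrols in UWS or MCS, and some will still be in one of these states during follow-up. If FIM is flat or nearly flat in those patients and spread out in the others, a model with FIM but not consciousness lets FIM stand in for consciousness. Participation and quality of life are also likely to be worse in unconscious patients. FIM could then pass the p < 0.05 screen and be read as a motor predictor even if motor function made no difference among patients of equal consciousness. The study aims to identify predictors of outcome in order to improve care, so a mislabelled predictor matters. The caregiver models show that the authors already regard consciousness and FIM as separate covariates.

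**Working it through.** **1. Score range.** The plan's range for the total is reproduced: 18 items × 1 = 18 and 18 × 7 = 126. The 13 motor items run from 13 × 1 = 13 to 13 × 7 = 91, and the 5 cognitive items from 5 to 35. Of the total's 108-point range, 35 − 5 = 30 points (28%) are cognitive. The article does not say whether the total or the motor items serve as motor status.

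**2. Where unconscious patients fall.** The lowest rating means total assistance, and in UWS no purposeful behaviour is seen. A total at or near 18 (motor items at or near 13) follows for UWS. For MCS the documents support only that low scores are plausible. The EIN programme section says these patients spend more time training mobility and self-care, so some may score above the minimum.

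**3. Covariate lists side by side.**

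| Model family | FIM | Level of consciousness |
|---|---|---|
| Quality of life, participation | yes | not listed |
| Caregiver self-efficacy, strain | yes | listed |

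**4. What the FIM coefficient estimates.** Take one visit, two states (conscious or not) and a linear model with FIM alone. Put every unconscious patient at 18, and let

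- p = share conscious
- m, s = mean and SD of FIM in conscious patients
- D = difference in mean outcome between the states
- β = FIM slope among conscious patients

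The between-state variance of FIM is b = p(1 − p)(m − 18)², and the within-state variance is w = p·s². Dividing total covariance by total variance gives

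slope = R · D/(m − 18) + (1 − R) · β, with R = b/(b + w).

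R is the share of FIM variance due to the consciousness difference, and also its weight in the slope. If β = 0, a fraction R of the whole outcome gap D is credited to FIM over the gap m − 18. With the state in the model, the slope is β.

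**5. Numbers.** The documents give none of p, m or s. Assumed ranges: p = 0.2 to 0.8, m = 40 to 80, s = 15 to 30.

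| p | m | s | b | w | R |
|---|---|---|---|---|---|
| 0.8 | 40 | 30 | 0.16 × 22² = 77.4 | 720 | 10% |
| 0.6 | 60 | 30 | 0.24 × 42² = 423.4 | 540 | 44% |
| 0.4 | 60 | 15 | 423.4 | 90 | 82% |
| 0.2 | 80 | 15 | 0.16 × 62² = 615.0 | 45 | 93% |

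The first and last rows are the extremes over the ranges. The middle rows bound the settings with m = 60 and p = 0.4 or 0.6. At unchanged means, any spread of FIM among unconscious patients adds to the within-state variance and lowers R.

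**The case against.** The strongest reply is that the one-by-one step is only a screen. The multivariable model is meant to test independence, and its candidates include the DRS, whose upper bands (22 and above) are labelled vegetative. This has force: the DRS partly encodes consciousness and may absorb some of the confounding. But it enters only if it passes the screen, none of its bands is labelled MCS, and it also measures general disability. It need not remove the mixing.

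A second reply is that if MoCA and HADS can be completed only by conscious patients, a multivariable model containing either would use conscious observations alone, and the contrast would vanish there. That is possible, but the measurement-plan figure is not shown. It would leave the screen affected, and the two stages would rest on different patients.

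Three stronger readings are tempting, but the documents do not support them:

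- **Motor status is measured only by FIM.** This is true of the model covariate, not of the study. The CRS-R has a motor subscale, the DRS includes motor response, and joint range of motion and the Modified Ashworth scale are recorded as complications.
- **Motor recovery would therefore be reported as absent.** This does not follow, since those other measures are collected and study parameters are reported descriptively.
- **FIM is nothing but a consciousness contrast.** FIM can vary up to 126 among recovered patients, and R stays below 100% even with every unconscious patient at the floor.

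Nor can the share at the floor be derived from the recovery percentages in the Background. Those count regaining minimal consciousness, which includes MCS, and one minus recovered would also count deaths, which supply no FIM score.

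**Conclusion.** The point holds as a limited, inexpensive improvement. In the quality-of-life and participation models, the screened FIM coefficient combines motor function with level of consciousness, and the plan omits there the covariate it uses for caregivers. The weight on consciousness is 10% to 93% under the assumed ranges, and about 44% to 82% in mid-range settings. These figures assume two states, a single visit and all unconscious patients exactly at 18, so they illustrate the problem and do not predict the trial's result. A floor in UWS follows from the protocol's definitions; a floor in MCS is not established. How much of the mixing survives the multivariable step cannot be fixed from the documents.

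**What to change.** - In the quality-of-life and participation models, enter level of consciousness (UWS, MCS, conscious) whenever FIM is entered, in the one-by-one step as well as the multivariable model. This matches the caregiver models. Alternatively, estimate the FIM effect among emerged patients only and label it so.
- Use the 13 FIM motor items (13 to 91) as motor status. The total contains 5 cognitive items, and cognition already has its own covariate, MoCA.
- Report the share of patients at the FIM floor at each visit, by level of consciousness.

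The CRS-R motor subscale could be described alongside for patients in UWS or MCS. Replacing FIM with it is debatable, because the CRS-R also defines level of consciousness.

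The cost is one extra model term, or fewer observations for the FIM effect if it is restricted to emerged patients. Level of consciousness and FIM are already collected, so no new measurement is needed.

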There are some limitations in this study that need to be discussed. First, as EIN is standard care a randomized controlled trial design is not feasible for ethical reasons. Second, LOC determination in PDOC is difficult in the absence of a gold standard. Recent guidelines advocate the use of additional diagnostic techniques such as EEG beside a behavioural assessment in the diagnostic process [26, 49]. However, to date these are not implemented in daily PDOC care in the Netherlands. In DOCTOR, we use the CRS-R, the most frequently used instrument worldwide [26]. While assessing LOC by using CRS-R, confounding factors such as motor, visual, auditory and/or cognitive impairments (e.g., language, memory, flexibility, attention) [50], intubation, sedation and the setting (e.g., presence or absence of relatives) should be taken into consideration [51], as they may negatively influence the diagnostic evaluation. Third, the follow-up time of our study is limited to 2 years. While some patients may show later recovery, the most significant proportion of recovery of consciousness after brain injury takes place in the first 1 to 1.5 years [48]. However, due to the high rate of misdiagnosis in PDOC, the evidence on ‘late’ recovery from PDOC may suffer from a diagnostic delay bias [52]. While most functional recovery occurs by 1-year post-injury, improvements may occur over a more prolonged interval. Some studies have shown significant improvement in cognitive and motor function in TBI patients admitted to inpatient rehabilitation from rehabilitation discharge to year 1, year 1 to 2, year 2 to 5 and year 5 to 10. However, the gains noted across functional areas by 2, 5 and 10 years after injury were relatively small compared with the first year post-injury [17, 53, 54]. Therefore, we think that a follow-up of 2 years will provide a good representation of the recovery after DOC in the long term, both for regaining consciousness and level of cognitive, behavioural, emotional and motor functioning.

To summarize, in this contribution we present the protocol of the DOCTOR study: a nationwide single-centre prospective cohort study of the outcomes of PDOC patients enrolled in Early Intensive Neurorehabilitation, followed up to 2 years after admission, which will provide insight in the long-term recovery patterns and predictors of multiple outcomes in patients with PDOC.

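### Time is listed as one of the candidates entered one by one, so time-varying predictors are screened without it, and a real predictor that works against a strong shared recovery trend can be lost

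*Protocol article*

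**What the plan says.** All of this is in the protocol article, Methods, Statistical analysis.

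- **Quality of life and participation (linear GEE).** The list of effects to be studied opens with time: "The effects of time, cognitive (MoCa), behavioural (NPI), emotional (HADS), and motor status (FIM), and level of disability (DRS) and discomfort (NCS"). The same sentence ends by saying that these effects "will be studied by adding these time-dependent variables (one by one) as independent variables to the models".
- **Recovery of consciousness (logistic GEE).** "Independent variables that will be added one by one to the models, include- measurement time (weeks), traumatic vs. non-traumatic aetiology, age at injury, and complications". The last of these may enter either as an indicator or as a count.
- **Selection.** In both sets, variables with p < 0.05 go forward. For quality of life and participation they "will be added into a multivariable GEE-model to study the independence of these potential predictors on the outcomes using the Bonferroni correction". For recovery the correction is defined as "dividing the significance level (alpha< 0.05) by the number of predictors included in the model".

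The article does not say that time stays in each one-by-one model, and it describes no step by which a variable that fails the screen can return.

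The Discussion expects change inside the 104-week follow-up: "the most significant proportion of recovery of consciousness after brain injury takes place in the first 1 to 1.5 years", and most functional recovery by one year after injury.

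**The concern.** Taken literally, the screening model for a time-varying candidate X is E[Y] = b0 + b1·X, with no term for time since admission. Where Y and X both move as patients recover, b1 combines two things: the association between X and Y at a given time, and the trend they share.

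This can go wrong in two ways.

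- A candidate with no association of its own can pass because it drifts with the outcome. The multivariable stage can put this right if time is in that model.
- A candidate whose real association runs against the shared trend can be cancelled in the screen and dropped, or can appear with the wrong sign in the one-by-one results. No later stage recovers a dropped variable.

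The candidates exposed are MoCA, NPI, HADS, FIM, DRS and NCS in the quality-of-life and participation models, and complications in the recovery models. Predictors of recovery and of multiple outcomes are a stated product of the study, so the selection rule affects what it will report.

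**Working it through.** **Inputs from the article.** Target of 72 patients (Data collection). Visits at start, weeks 5 and 10, discharge (at most week 14), and weeks 28, 40, 52 and 104. Screening threshold 0.05. Second-stage threshold 0.05/k for k predictors: 0.05/2 = 0.025 for one predictor plus time, 0.05/4 = 0.0125 if all four recovery candidates enter, 0.05/7 = 0.0071 if all seven quality-of-life candidates enter. The article gives no power calculation, effect size or trend size, so there is no figure of its own to reproduce.

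**Assumptions.** Linear GEE, exchangeable working correlation, robust standard errors, 72 patients, six visits (weeks 0, 14, 28, 40, 52, 104), no dropout, within-patient correlation ρ = 0.5, predictor and outcome of unit SD before trend and effect, trend proportional to the square root of time; 2,000 runs per setting. Trend size τ is the SD of the visit means. For these visits the SD of √(week/104) is 0.308, so the rise from week 0 to week 104 is τ/0.308 = 3.25τ: τ = 0.2, 0.3 and 0.4 mean rises of 0.65, 0.98 and 1.30 SD. The outcome trend is the part not due to the predictor.

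**Step 1: what the screen estimates.** With outcome trend τy, predictor trend τx and true effect β, the coefficient without time is approximately

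b1 = β + τy·τx / [(1 − ρ) + τx²].

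| β | τy = τx | Formula | Simulated mean |
|---|---|---|---|
| 0 | 0.2 | 0.04/0.54 = 0.074 | 0.073 |
| 0 | 0.4 | 0.16/0.66 = 0.242 | 0.239 |
| -0.2 | 0.2 | -0.2 + 0.074 = -0.126 | -0.126 |
| -0.2 | 0.3 | -0.2 + 0.09/0.59 = -0.047 | -0.052 |
| -0.2 | 0.4 | -0.2 + 0.242 = 0.042 | 0.037 |

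For β = -0.2 and equal trends, cancellation is complete when τ²/(0.5 + τ²) = 0.2, so τ² = 0.1/0.8 = 0.125 and τ = 0.354, a rise of about 1.15 SD. Beyond that point the sign reverses.

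**Step 2: chance of passing.** The last column applies both stages: the screen at 0.05, then 0.025 in the model with time when time also passes.

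| β | τy | τx | Screen without time | Screen with time | After both stages |
|---|---|---|---|---|---|
| 0 | 0 | 0 | 6% | 6% | 6% |
| 0 | 0.2 | 0.2 | 34% | 5% | 1.5% |
| 0 | 0.4 | 0.4 | 100% | 6% | 3% |
| -0.2 | 0.2 | 0.2 | 77% | 98% | 77% |
| -0.2 | 0.3 | 0.3 | 21% | 99% | 21% |
| -0.2 | 0.4 | 0.4 | 15% (14 points wrong sign) | 98% | 12% |
| -0.2 | 0.6 | 0.4 | 83% (all wrong sign) | 99% | 81% |
| -0.2 | 0.4 | 0 | 96% | 99% | 95% |

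The last row is the control: with no trend in the predictor, little is lost. The row above it shows that loss does not keep growing with the trend. It is worst near cancellation. Past that, the predictor passes with the wrong sign and the model with time then restores the sign.

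**Step 3: later visits only.** At weeks 28 to 104, with 72 patients and a true effect of -0.25, a separate linear simulation gave passing rates of 84%, 30% and 22% at shared rises of 0.5, 0.8 and 1.2 SD (all wrong-signed at 1.2), against 98-99% with time. A null predictor passed in 15%, 63% and 100% of runs, against about 5-6%. At a shared linear trend of 0.3 SD the false-positive rate of the screen was about 6%.

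**The case against.** **Another reading.** Both GEE paragraphs speak of the course over time, and variables are added to the models, which could mean that a base model already holds time or that entry is cumulative starting with time. This does not fit sentences that list time among the things being added. If it was intended, the wording still needs correcting. Nor is this a detail left to a fuller plan: the rule is stated.

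**Scope.** A reader might infer that the shared trend decides which predictors survive, or that every candidate is affected. The documents do not support that.
- Aetiology and age at injury are fixed, so a shared trend does not confound them in this way.
- Better MoCA, FIM and DRS scores would be expected to move with recovery and with better outcomes. A real predictor aligned with the trend passes in about 100% of simulated runs.
- Loss requires a real effect against a strong trend. HADS, NPI or a cumulative complication count are possible examples, but the article does not say that any of them rises as patients recover, or that the count is cumulative.

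**Wrong inclusions.** These are largely corrected at the second stage, and where the trend is large enough to matter time nearly always passes too. This stands, and it limits the practical weight of time having to pass the screen.

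**Size.** The rates rest on assumed trends and effects. With another way of specifying the outcome trend, passing rates at weeks 28 to 104 were 88% and 49% at rises of 0.5 and 0.8 SD, so loss at 0.8 SD is real but its size is uncertain. The Discussion also calls gains after the first year relatively small, which argues for weaker trends at late visits. All simulations are linear; none covers the logistic recovery models.

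**Conclusion.** The point holds in limited form. As written, time-varying candidates are screened at p < 0.05 without time, and time has to earn its place. The screen can then admit null predictors, most of which the second stage removes if time is kept. It can also reject a real predictor that opposes a strong shared trend, with no route back, or show it with the wrong sign in the one-by-one results.

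Under the stated assumptions the chance that such a predictor survives the screen falls from 98-99% to between 15% and 77% for shared rises of about 0.65 to 1.3 SD. At about 0.3 SD or less the harm is small. These figures illustrate the mechanism and do not forecast this study's results. The with-time figures in the main simulation also use the same trend shape as the simulated data, which is the favourable case.

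The mechanism carries over in principle to complications in the recovery models, but the rates do not transfer directly. The time at issue is time since admission, that is, recovery itself, so the results should not be described as driven by calendar drift. The correction is worth making because it is cheap and affects a stated product of the study.

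**What to change.** In Statistical analysis, state that measurement time is a fixed term in every screening and multivariable GEE model, whatever its p-value. Each other candidate is then screened as E[Y] = b0 + f(time) + b1·X, with the logit of the probability of recovery on the left-hand side in the recovery models. Remove time from the list of candidates and report its effect as the course over time. Say whether time counts towards the Bonferroni divisor, since that divisor is the number of predictors in the model.

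The cost is a sentence or two of wording, no new data, one extra term per model (a few if visits are entered as categories), and a small loss of precision where there is no trend.
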